Within the Welsh NHS Stop Smoking Service^a^, various service improvements have occurred since 2009 with a view to strengthening the referral system for pregnant women who smoke from antenatal units to the stop smoking service. These service improvements have included additional training of midwifery staff, in line with National Institute for Health and Care Excellence (NICE) guidance, to encourage the use of CO testing. Despite this, referrals into the service and engagement with pregnant women has continued to remain extremely low. For example, data from the Stop Smoking Service show that in the referral period May 2012-March 2013, 1,817 pregnant smokers were referred to the service from maternity services, but only 529 went on to accept an appointment. At this time, there were around 32,000 births in Wales [9] based on a smoking prevalence of 33% [1], 5.6% of smokers were referred to the service, and 1.6% of smokers accepted an appointment. In response, key partners were brought together across Wales to develop a public health study, Models for Access to Maternal Smoking cessation Support (MAMSS) with the aim of testing the effectiveness of three different models of service delivery to address the gap in the evidence base about how to deliver a flexible tailored smoking cessation service to pregnant women.

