**Recruitment flow diagram.**

In intervention sites, pregnant smokers will be referred to one of three different models of service delivery where smoking cessation services are provided by maternity support workers, midwives or smoking cessation advisors dedicated to working with pregnant women, all offering a flexible service designed to meet the needs of the women. The core elements of the evidence base to be implemented in all intervention sites will include:

 Strict adherence to NICE opt out smoking cessation pathway for pregnant women, including CO monitoring. Smoking cessation services being more closely aligned to maternity services (provided as part of the package of maternity care). Referral from midwife to smoking cessation support within 48 hours Flexibility in service model with a women centred approach.

Each intervention site will recruit a whole-time equivalent (WTE) maternity support worker (employed by the Health Board), midwife (employed by the Health Board) or dedicated Stop Smoking Advisor for pregnant women (employed by the NHS Stop Smoking Service) who will deliver stop smoking support to pregnant women. These staff will receive referrals directly from midwives to provide an intensive smoking cessation intervention at times and settings of the women’s choice, including home visits. During every subsequent antenatal appointment, women will be asked about their smoking status and referred as appropriate. If a woman has declined treatment (i.e. she opts-out by not answering the telephone to stop smoking services or refuses an assessment appointment) she will be asked if she would like to be re-referred during each follow-up appointment.

Clients in intervention sites will be offered smoking cessation support for the duration of their pregnancy if required. The support they receive will follow an adapted behavioural intervention model documented in the NHS Stop Smoking Service delivery manual, which is based on withdrawal oriented therapy (Maudsley model) [12]. This may involve a combination of telephone and face to face support as well as motivational support by email and or text, dependent upon the needs of the client (see Figure 1). A detailed manual for specialist smoking cessation staff has been developed for use in all intervention sites detailing the referral pathway, intervention programme, policies, procedures and support materials.

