### Outcome measures

The primary outcome measure is engagement with stop smoking services (defined as having at least one face-to-face therapeutic contact with an advisor) and secondary outcome measures are pregnant smokers who set a quit date; pregnant smokers who quit at four weeks follow-up (CO verified); smoking status at the time of birth or third trimester and 52 weeks; and birth outcomes (low birth weight (<2500 g), preterm birth <37 weeks).

Process measures will assess fidelity to protocols, feasibility, acceptability, maintenance and sustainability should the interventions be rolled out on a wider scale. Data will be obtained from available data sources within maternity services and the NHS Stop Smoking Service on specific aspects of the referral pathway and treatment programme.

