### Analysis

Baseline demographic and social characteristics of pregnant smokers in both intervention and usual care sites will be summarised using descriptive statistics. Comparisons between the two groups will be carried out using a Student’s *t*-test or a non-parametric test for continuous data and a chi-squared test or a Fisher’s exact test for categorical data. Characteristics of women who do not opt out of the referral will be compared to those who do. Continuous data will be expressed as mean values with standard deviations and categorical data will be presented as counts with percentages. A single logistic regression model will be developed to obtain odds ratios for the comparison of different interventions with usual care, and for comparisons between interventions. Differences in baseline characteristics of individuals and referral rates for Stop Smoking Services will be adjusted for. To account for the geographical clustering of individuals, robust standard errors will be calculated.

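### The model comparing interventions with usual care adjusts for referral rates without limiting them to pre-study rates; a study-period rate can itself be changed by the intervention

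*Protocol article*

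**What the plan says.** The Analysis section of the protocol article describes one model for the effect estimates: "A single logistic regression model will be developed to obtain odds ratios for the comparison of different interventions with usual care", and also for comparisons between interventions. Its adjustment rule is: "Differences in baseline characteristics of individuals and referral rates for Stop Smoking Services will be adjusted for". In that sentence the word baseline attaches to the characteristics of individuals. The referral rates carry no time reference and no level (woman or site).

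The primary outcome, under Outcome measures, is "engagement with stop smoking services (defined as having at least one face-to-face therapeutic contact with an advisor"). Eligibility, under Sample, covers pregnant smokers and recent quitters under midwifery care and is not restricted to women who were referred.

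The Interventions section (text after the recruitment flow diagram) lists these among the elements for intervention sites:
- "Strict adherence to NICE opt out smoking cessation pathway for pregnant women, including CO monitoring"
- "Referral from midwife to smoking cessation support within 48 hours"

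It adds that staff there take referrals directly from midwives, and then: "During every subsequent antenatal appointment, women will be asked about their smoking status and referred as appropriate". For a woman who has declined treatment, "she will be asked if she would like to be re-referred during each follow-up appointment".

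Usual care also uses opt-out referral (Interventions; Comparison group). The Abstract says that core guidance is implemented in both kinds of site and that the difference is more flexible delivery.

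**The concern.** A woman has to be identified and referred before she can have a face-to-face contact with the service. If the service model changes how many women are referred, the referral rate during the study is a step between exposure and outcome, not a confounder. Conditioning on it takes out whatever part of the effect runs through referral.

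The sample-size hypothesis concerns engagement among pregnant smokers, which is the total effect. The Background gives the motive for the study in terms of both steps: "referrals into the service and engagement with pregnant women has continued to remain extremely low". A model that holds study-period referral fixed answers a narrower question, namely whether the service engages more women at a given level of referral. A service that works partly by getting more women referred would look weaker than it is.

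This is also a non-randomised comparison of self-selected Health Boards. A referral rate from before the study could be a legitimate confounder. The two readings of the sentence therefore point to different models and different effects.

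**Working it through.** **1. The plan's own figure.** Inputs (Sample size section): 10% versus 25%, type I error 5%, power 90%. The mean proportion is 0.175.

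Two-sided, uncorrected: n = [1.96·√(2·0.175·0.825) + 1.2816·√(0.10·0.90 + 0.25·0.75)]² / 0.15² = 132.8, so 133 per group.

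With continuity correction: n = (132.8/4)·[1 + √(1 + 4/(132.8·0.15))]² = 145.8, so 146. This reproduces the stated 146 per group within each Health Board. By the uncorrected formula, 146 per group gives 92.5% power. The point made here does not alter this figure.

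**2. Planned total effect.** OR = (0.25/0.75)/(0.10/0.90) = 3.0.

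**3. Effect with referral held fixed.** Let r be the share of eligible women referred and q the share of referred women who engage, and assume that no one engages without referral. Then engagement = r·q, so q = 0.10/r in usual care and 0.25/r in intervention. The documents give no referral rate by arm, so the rates below are assumptions, shown as a range. Power is for one Health Board, among referred women only (146·r per group), by the uncorrected formula.

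| Referral, usual care / intervention (assumed) | q, usual care | q, intervention | OR, referral fixed | Share of log OR removed | Power |
|---|---|---|---|---|---|
| 90% / 90% | 0.111 | 0.278 | 3.08 | none | 93% |
| 85% / 95% | 0.118 | 0.263 | 2.68 | 10% | 85% |
| 80% / 95% | 0.125 | 0.263 | 2.50 | 17% | 79% |
| 70% / 90% | 0.143 | 0.278 | 2.31 | 24% | 71% |
| 50% / 90% | 0.200 | 0.278 | 1.54 | 61% | 23% |

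Example, 70%/90%: (0.278/0.722)/(0.143/0.857) = 0.385/0.167 = 2.31, and 1 − ln 2.31/ln 3.0 = 0.24.

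**4. If the rate enters at site level.** One intervention and one usual-care site in each of four Health Boards gives 4 × 2 = 8 sites, hence at most eight distinct rates. A simulation took eight sites of 146 women. Site referral rates varied around the arm mean with an SD of 5 percentage points, the three service models were pooled into one intervention arm, and there were 1,500 replicates per row. The observed site rate was the covariate.

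| Referral (assumed) | Median OR, unadjusted | Median OR, adjusted | SD of log OR, unadjusted | SD of log OR, adjusted |
|---|---|---|---|---|
| 85% / 85% | 3.01 | 3.03 | 0.18 | 0.19 |
| 85% / 95% | 2.99 | 2.59 | 0.17 | 0.30 |
| 70% / 90% | 3.00 | 2.18 | 0.17 | 0.40 |
| 50% / 90% | 3.03 | 1.51 | 0.18 | 0.76 |

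The attenuation matches step 3, and the spread of the estimate grows as the site rates separate by arm. The planned model has three intervention terms. With an intercept and a site-level referral rate that makes five parameters, leaving 8 − 5 = 3 site-level degrees of freedom. If each intervention site runs one model and all three models are used, two of the three models rest on a single site.

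**The case against.** The sentence in the Analysis section does not say that the rates come from the study period. Service records from before the study exist (the Background cites counts for May 2012 to March 2013), and a pre-study rate is a proper adjustment in a design like this. The article condenses a fuller plan, and the section on quantitative data collection refers to an agreed analysis plan, where covariates might be defined. This stands as a reason not to call the adjustment wrong under every reading. It does not remove the point: the adjustment is a stated rule, and as worded it admits a post-exposure covariate.

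A reader might infer that the intervention is designed to raise the referral rate, so that part of the effect is bound to be lost. The documents do not support that. Opt-out referral and core guidance apply in both arms, and the declared contrast is flexibility. The 48-hour element concerns speed, and the re-referral offer concerns women already referred, so neither need change the share ever referred. The stronger evidence is strict adherence with CO monitoring, direct midwife referral, and asking and referring at every later visit. These make a difference between arms possible, not certain.

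A reader might also take the Background counts (1,817 referred out of 32,000 × 0.33 = 10,560 smokers, or 17.2%; the text itself prints 5.6%), suppose that referral rises to, say, 60% with uptake after referral unchanged, and conclude that adjustment drives the odds ratio to about 1. That result follows by construction. It keeps usual care at a historical rate although usual care is also opt-out, it assumes away any benefit of flexible delivery, and it rests on accepted appointments, not face-to-face contacts.

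Nor do the documents show that referral is strongly aligned with arm, or that the covariate is at site level. The loss of precision in step 4 depends on both.

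**Conclusion.** The concern holds in a conditional form. The only model described for comparing interventions with usual care adjusts for differences in referral rates, does not restrict these to the pre-study period, and sits beside an intervention package with referral steps of its own. If the rate is measured during the study, the odds ratio describes the effect with referral held fixed.

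The size depends on the gap in referral between arms. Nothing is lost when the rates are equal. Starting from OR 3.0, the estimate falls to about 2.7 at 85%/95%, 2.3 at 70%/90% and 1.5 at 50%/90%. These pairs are assumptions, as is the premise that engagement requires referral. If the rate is a site-level covariate, the SD of the log OR rises from about 0.18 to 0.30, 0.40 and 0.76 in the same three cases.

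The wording should be settled before the data are analysed, because the two readings target different effects for the primary outcome.

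**What to change.** Replace the adjustment sentence in the Analysis section so that:
- the primary model adjusts for individual baseline characteristics and contains no referral rate measured during the study;
- if differences in referral practice between sites are the concern, each site's pre-study referral rate is used, where the service records can supply it, with its period and level stated;
- study-period referral is reported by site as a process outcome;
- a model adjusted for study-period referral is kept only as a secondary analysis, labelled as the effect with referral held fixed.

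Simply deleting referral without considering the pre-study rate could drop a valid confounder.

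The cost is a sentence or two and, if the pre-study rate is used, one extract from existing service records. The downside is that the primary odds ratio then includes any effect through referral and does not isolate flexible delivery alone. The secondary model addresses that question.

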## Methods

This study will be undertaken as a quasi-experimental design. Donabedian’s conceptual model for examining health services and evaluating quality of care as a framework for examining structures, processes and outcomes will be applied [10]. The setting will be four of Wales’ seven Health Boards. These are single local health organisations responsible for planning, securing and delivering all healthcare services within a geographical area. The Health Boards involved in the study are self-selected and are geographically diverse. Total population figures range from 294,497 to 690,434 [11] and live births range from 63.9 to 66.3 per 1000 women aged 15-44 [9] (see Table 1).

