### Interventions

The study will take place over 12 months using an integrated approach between maternity services, local public health teams and the NHS Stop Smoking Service. In each Health Board, an intervention and a usual care site will be selected from existing community midwifery teams. Sites will be selected on the basis of high rates of pregnant smokers, and a similar demographic profile in intervention and usual care sites within each Health Board. Pregnant smokers (i.e. those who are self-reported current smokers or have a CO reading # 7 ppm^b,^^c^ or who have quit in the two weeks prior to their booking appointment [5]) will be referred to the intervention or usual care NHS Stop Smoking Service on an opt out basis (see Figures 1 and 2). This automatically refers pregnant smokers to the service. The two main points for referral are the first antenatal appointment (at home or in a community antenatal clinic by the midwife) or subsequent scheduled antenatal care visits (by the midwife). However, the referral process can take place at any stage during pregnancy, for example, during the postpartum period whilst under the care of a midwife.

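### Robust standard errors cannot support five of the six planned model contrasts, because two of the three service models rest on a single site each

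*Protocol article*

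**What the plan says.** - Protocol article, Methods: "The setting will be four of Wales’ seven Health Boards", and "This study will be undertaken as a quasi-experimental design".
- Interventions: "In each Health Board, an intervention and a usual care site will be selected from existing community midwifery teams". This gives 4 + 4 = 8 sites.
- Interventions, text on intervention sites: "pregnant smokers will be referred to one of three different models of service delivery". Each site is tied to one kind of worker: "Each intervention site will recruit a whole-time equivalent (WTE) maternity support worker (employed by the Health Board), midwife (employed by the Health Board) or dedicated". The third option, cut off there, is an adviser from the national cessation service.
- Analysis: "A single logistic regression model will be developed to obtain odds ratios for the comparison of different interventions with usual care, and for comparisons between". The sentence closes by naming the models, so contrasts of one model with another are planned too. Baseline characteristics and referral rates are to be adjusted for.
- Analysis, on clustering: "To account for the geographical clustering of individuals, robust standard errors will be calculated". No cluster unit, small-sample correction or reference distribution is named.
- Sample size: 146 pregnant smokers per group within each Health Board, for 10% against 25% engagement, 5% type I error and 90% power.

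**The concern.** A cluster-robust variance learns about between-cluster variation from the scatter of cluster residual totals. It needs several clusters behind every coefficient. Here two of the three model coefficients have one site behind them. The fitted coefficient reproduces that site's rate, the site's residuals cancel, and the site appears to contribute no uncertainty.

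The stakes are high because the study exists to compare models and to learn who should provide the service, and engagement is the primary outcome. An ordinary difference between two midwifery teams could be reported as the superiority of one provider type, with a confidence interval that is far too narrow.

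**Working it through.** **Stated figure.** Two-sided 5%, 90% power, 10% v 25%, mean 17.5%: n = [1.96√(2×0.175×0.825) + 1.2816√(0.09 + 0.1875)]² / 0.15² = 132.8, so 133. With continuity correction, (132.8/4)[1 + √(1 + 4/(132.8×0.15))]² = 145.8, so 146. The figure reproduces. It is an individual-level calculation with no design effect.

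**Layout.** There are four usual-care sites (U) and four intervention sites over three models: A (1 site), B (1 site), C (2 sites). The six contrasts are A–U, B–U, C–U, A–B, A–C and B–C. All except C–U involve a single-site model.

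**Why the variance fails.** Without covariates, the site-clustered variance of group k's log odds is G/(G−1) × Σ(yᵢ − m·p̂ₖ)² / [Nₖp̂ₖ(1−p̂ₖ)]², summed over its sites. Here m is the women per site and Nₖ the women in the group. With one site, yᵢ = m·p̂ₖ, so the sum is zero. For A–B both parts vanish and the standard error is exactly zero.

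**Size, by hand.** Let a site-level estimate have total variance σ², treat it as approximately normal, and use the factor 8/7.
- A–U: the true variance is σ²(1 + 1/4) = 1.25σ². The sandwich has expectation (8/7)(3/16)σ² = 0.214σ², so the reported standard error is about √(0.214/1.25) = 0.41 of the true one. Rejection is P(|t₃| > 1.96×0.414) = 0.48. With t(7) it is P(|t₃| > 2.365×0.414) = 0.40.
- A–C: true 1.5σ², sandwich (8/7)(1/4)σ² = 0.286σ², ratio 0.436. P(|t₁| > 1.96×0.436) = 0.55.

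σ² cancels, so these rates hardly depend on the ICC.

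**Size, by simulation.** No true effect, 8 sites of 146 women, beta-binomial site rates, 40,000 runs per setting, clustering by site. The ICC is not in the documents and was assumed at 0.005–0.05.

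| Contrast | normal reference | t(7) |
|---|---|---|
| Single-site v usual care | 48–51% | 40–44% |
| Single-site v two-site | 55–57% | 49–51% |
| Single-site v single-site, no covariates | 94–97% | the same (zero SE) |
| Two-site v usual care | 21–22% | 14–17% |

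**Variants.**
- Individual covariates: A–U 47–50%. A–B was 83–91% in one set of runs (about 400 per setting) and 94–96% in another (600 per setting).
- A site-level covariate, as a referral rate would naturally be: A–B falls to about 71%, A–U stays near 50%, C–U rises to about 30%.
- Clustering by Health Board: A–U 45–48% (normal) or 26–28% (t on 3 df).
- Errors that ignore site: design effect D = 1 + 145×ICC, and rejection is 2[1 − Φ(1.96/√D)]. This gives 14% at ICC 0.005 (D = 1.725), 21% at 0.01 (2.45), 32% at 0.02 (3.9) and 49% at 0.05 (8.25). Simulation agrees: 12–13%, 19–21%, 30–33% and 47–50%.

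**Valid benchmarks.** A t-test of one site against the four usual-care sites (3 df) rejects in 5–6%. A paired t-test on the four within-Board differences (3 df) rejects in 4–5%.

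**The case against.** The strongest reply is that the article names no cluster unit, correction or reference distribution, that such detail commonly sits in an analysis plan, and that the article mentions an agreed plan which is not shown. This stands as a limit on the figures: each is conditional on a choice the article does not state. It does not remove the defect. No cluster unit or correction can separate model from site when a model has one site, and the commitment to between-model odds ratios is already made in the article.

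A reader might go further and infer that all the planned tests reject by chance half the time or more. The documents do not support that:
- The two-site model against usual care is one of the six contrasts and rejects in about 20%. A pooled comparison would reject in about 12–15%, but it is not among the stated contrasts.
- Rates near 95% between two single-site models do not describe the planned adjusted analysis, where a site-level covariate brings the rate to about 71%. Without covariates, a standard error of zero would also be noticed as broken output.
- With errors that ignore site, a rate near half needs an ICC of about 0.05, for which the documents give no basis.

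Nor does the text establish that each single-site model depends on one person. "Each intervention site will recruit a whole-time equivalent (WTE) maternity support worker" and the alternatives that follow it fix an amount of staffing, which could be shared.

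**Conclusion.** The point holds in this limited form. The stated method is wrong for the five contrasts that involve a single-site model, and it is anti-conservative for the sixth. Under site clustering with a normal reference, nominal 5% tests reject a true null in about 50% (single-site v usual care; 40–44% with t(7)), about 55% (single-site v two-site), roughly 70–97% (between single-site models, depending on covariates) and about 20% (two-site v usual care). If the errors ignore site, the range is about 12–13% at an assumed ICC of 0.005 to about 50% at 0.05.

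The 2/1/1 split rests on one worker type per intervention site and all three models being used, which is the plain reading of the text. The simulations assume 146 women per site and 10% engagement. Every variant with between-site variation clearly exceeded 5%. This should be corrected before analysis, since these contrasts answer the study's main question on its primary outcome.

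**What to change.** Replace the robust-standard-error tests with site-level inference:
1. Compare each model with usual care using covariate-adjusted site proportions and a t-distribution on the degrees of freedom available. For a single-site model that is one site against four, 3 df. State the assumption that the model's site varies as the usual-care sites do.
2. Add an overall contrast of flexible service against usual care from the four within-Health-Board differences (t, 3 df). Keep the model-specific results beside it, since the aim is to test three models.
3. Report contrasts between the two single-site models descriptively, without p-values, and say that model and site are confounded.

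The change is to the analysis wording and to the claims made, not to data collection. The costs are wider intervals and no formal test between single-site models. Power for 10% v 25% on the paired test, assuming no within-pair correlation, is about 92% at ICC 0.005, 82% at 0.01, 65% at 0.02 and 39% at 0.05, so the 90% in the Sample size section needs qualifying. Single-site tests will be weaker still. With equal site variances, their standard error is √(1.25σ²/0.5σ²) = 1.58 times that of the paired contrast, on the same 3 df. Site-level tests cover chance variation between sites. They do not remove bias from non-random choice of sites.
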